## Abstract

**Background:**

Both human genes and environmental exposures, due to complex interplay, play important role in the cancer etiology. Vitamin D is associated with a reduced risk of incidence and mortality of several human cancers. This study will aim to investigate the possible effects of individual polymorphisms in vitamin D receptor (*VDR*) as well as effects of *VDR* haplotypes on response to vitamin D supplementation in breast cancer survivors.

**Methods:**

This is an interventional study in which the effects of vitamin D supplementation on plasma vitamin D levels, inflammatory and antioxidant biomarkers and factors associated with cell proliferation, differentiation, damage, and apoptosis will be investigated stratified by variations in *VDR* genotype. The present study will be conducted on breast cancer survivors referred to the Shohadaye Tajrish hospital and its associated clinics. One hundred ninety-eight breast cancer survivors will receive 4000 IU of vitamin D3 daily for 12 weeks. *VDR* Fok1, ApaI, TaqI, BsmI, and Cdx-2 genotype will be determined at the end of the study and responses to vitamin D supplements (inflammatory, antioxidant, cell proliferation, differentiation, damage, and apoptosis biomarkers) will be compared between the three subgroups of each *VDR* polymorphism as well as different *VDR* haplotype categories.

**Discussion:**

Genetic variation is a fundamental factor influencing individuals’ divergent responses to diet, nutritional status, metabolic response, and diet-related health disorders. Furthermore, studies of gene and environment interactions will provide a precise and accurate assessments of individuals’ dietary requirements by considering both the genetic and environmental aspects simultaneously. The results of the current study, to some extent, will highlight the discrepancies existing in the findings of different studies regarding vitamin D, *VDR*, and cancer by considering both the genetic and environmental aspects simultaneously. If responses to vitamin D supplementation could be modified by *VDR* SNPs, determining the distribution of *VDR* polymorphisms in both breast cancer survivors and healthy populations will provide a new insight into the vitamin D requirements of individuals to prevent cancer and its related mortality based on their genotypes.

*Trial registration* This trial has been registered on Iranian Registry of Clinical Trials (IRCT) under the identification code: IRCT2017091736244N1, registration date: 2017-11-10, http://www.irct.ir/trial/27153

## Background

Cancer is one of the major multifactorial health problems over the last decades due to increased life span, the epidemiologic transition, and individuals being exposed to various risk factors for a long period [1]. Breast cancer is one of the most frequently diagnosed malignancies, accounting for 25.1% of all tumors, and is the second leading cause of cancer death in women worldwide [1, 2]. Higher incidence rates of breast cancer have also been reported in developed countries [1]. Risk factors for developing breast cancer include increasing age, family history of first-degree relatives with breast cancer, race, the mutation in *BRCA1* and *BRCA2* genes, menarche history, nulliparity, breast characteristics, hormone use, alcohol and tobacco use, dietary habits, physical activity, and obesity [2, 3].

Low vitamin D is associated with an incidence and mortality of several cancers [4, 5]. Increased risk for up to 15 prevalent cancer, including breast carcinoma, has been documented by several epidemiologic studies [4, 6–9]. Although the exact mechanisms by which vitamin D3 reduces the risk of cancer are unknown, it has been postulated that 1,25-dihydroxy vitamin D3 (1,25(OH)2D3), the active form of vitamin D3, has anti-proliferative, anti-angiogenic, pro-apoptotic [10], and anti-inflammatory properties [11] in many cells, including breast cancer cells. In addition, terminal cell proliferation, induced by 1,25(OH)2D3, resulted in declining growth and spread of malignant cells growth and spread [12].

1,25(OH)2D3 is locally produced in mammary tissue via conversion of circulating 25-hydroxyvitamin D3(25(OH)D) to 1,25(OH)2D3 by endogenous 1-α-hydroxylase in the breast [13]. The physiological effects of vitamin D3 are mostly modulated via the binding of 1,25–1,25(OH)2D3 to the vitamin D receptor (*VDR*) [14]. *VDR*, a nuclear hormone receptor superfamily member, encoded by a large gene located on chromosome 12cen-q12, containing at least five promoter regions, eight coding exons, and six untranslated exons [15]. *VDR* has been identified in many organs, including normal breast tissue and most breast tumors [16]. Transcription of several genes involved in cellular growth, differentiation, apoptosis, angiogenesis, inflammation [17], and metastasis is regulated via *VDR* [16].

Anticancer properties of vitamin D_3_ postulated that sequence level variations in the *VDR* gene may alter breast cancer risk either exclusively or via gene–gene or gene–environment interactions [18]. Findings of preliminary studies indicate that allelic differences in Fok1, Bsm1, Taq1, Apa1, EcoRV, and Cdx2 were the most frequent single-nucleotide polymorphisms (SNPs) correlated with malignancies [17, 19]. Meta-analysis studies on the association between *VDR* polymorphisms and breast cancer risk are inconsistent [19–24]. However, data from descriptive studies in which various effects of environmental exposures, e.g., vitamin D intake, plasma vitamin D status, etc., on breast cancer risk in persons with different genotypes were overlooked, which may account for discrepancies observed among the studies.

This will be the first study designed to evaluate the possible role of individual polymorphisms in *VDR* and to conduct an extensive analysis of *VDR* haplotypes on different aspects of responses of breast cancer survivors, i.e., inflammatory, oxidative stress, and metabolic biomarkers, biomarkers associated with cell proliferation, differentiation, damage, apoptosis, and anthropometric measures to daily supplementation of 4000 international unit (IU) vitamin D for 12 weeks.

## Objectives

### Primary objectives

To compare plasma 25-hydroxy vitamin D_3_(25(OH) D_3_) within and between polymorphic groups (Fok1, Bsm1, Taq1, Apa1, and Cdx2) in breast cancer survivors, adjusted for potential confounders.To compare plasma 25-hydroxy vitamin 25(OH) D_3_within and between haplotype groups in breast cancer survivors, adjusted for potential confounders.

### Secondary objective

To compare inflammatory, oxidative stress, and metabolic biomarkers, biomarkers associated with cell proliferation, differentiation, damage, apoptosis, and anthropometric measures within and between polymorphic groups (Fok1, Bsm1, Taq1, Apa1, and Cdx2) in breast cancer survivors, adjusted for potential confounders**.**To compare inflammatory, oxidative stress, and metabolic biomarkers, biomarkers associated with cell proliferation, differentiation, damage, apoptosis, and anthropometric measures within and between haplotype groups in breast cancer survivors adjusted for potential confounders.To perform an investigational analysis of mean changes in inflammatory, oxidative stress, and metabolic biomarkers, biomarkers associated with cell proliferation, differentiation, damage, apoptosis, and anthropometric measures based on VDR single-nucleotide polymorphisms (SNPs), i.e., Fok1, Bsm1, Taq1, Apa1, and Cdx2.

To perform an investigational analysis of mean changes in inflammatory, oxidative stress, and metabolic biomarkers, biomarkers associated with cell proliferation, differentiation, damage, apoptosis, and anthropometric measures in different haplotype groups.

### Hypothesis

Daily supplementation of vitamin D3 will ameliorate circulating 25(OH)D concentrations in breast cancer survivors.Daily supplementation of vitamin D3 will improve inflammatory, oxidative stress, and metabolic biomarkers, biomarkers associated with cell proliferation, differentiation, damage, apoptosis, and anthropometric measures in breast cancer survivors.Response to daily supplementation of vitamin D3 will vary between different *VDR* polymorphic groups.Response to daily supplementation of vitamin D3 will vary between different *VDR* haplotype groups.

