## Methods/Design

### Study design

This will be a 3-month clinical trial conducted on breast cancer survivors to assess the potential effects of vitamin D3 supplement on plasma vitamin D levels, inflammatory and antioxidant biomarkers, and factors associated with cell proliferation, differentiation, damage, and apoptosis based on polymorphic variation in VDR gene. The intervention period will be limited to the winter months (February, April) and spring months (May, June) to reduce dermal vitamin D synthesis. The current study will be accomplished by collaboration between the Faculty of Nutrition Sciences and Food Technology and the National Nutrition and Food Technology Research, the Cancer Research Center, and the Research Institute for Endocrine Sciences, Shahid Beheshti University of Medical Sciences.

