#### Intervention

One hundred ninety-eight breast cancer survivors will receive 4000 IU of vitamin D_3_ daily for 12 weeks (cholecalciferol tablets will be manufactured by *JALINOUS PHARMACEUTICAL* CO, Tehran, Iran). Subjects will be given 84 pills at the beginning of the study and will be instructed to consume one tablet with one of their daily meals. Participant compliance will be assessed through biweekly telephone calls. The intervention period will be 12 weeks. Health-related benefits of vitamin D without any increase in the risk of health problems have been demonstrated by plasma 25(OH)D levels of 75–110 nmol/l, achieved through daily supplementation of vitamin D_3_ in the range of 1800–4000 IU [25]. Anthropometric measurement, body composition analysis, dietary, physical activity, and laboratory assessments will be carried out before and after supplementation, and outcomes of interest will be compared between variant *VDR* polymorphic groups.

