### Laboratory assessment

#### Blood sampling

Fasting venous blood samples (15 ml) will be taken in spring (April–May) and winter (February–March) from all participants in a sitting position by phlebotomy. Blood sample will be divided in two tubes: (1) a plastic tube with an anticoagulant, EDTA (Ethylenediaminetetraacetic acid); (2) a plastic tube with an anticoagulant, EDTA and anti-protease. Blood collection tubes will be tagged with identification codes; the tubes containing the EDTA blood sample will be centrifuged at 3000×*g* for 10 min for white blood cell (WBC) separation, while the tubes containing EDTA and anti-protease blood sample will be centrifuged for plasma separation. Obtained plasma will be distributed in clean micro-tubes and will be kept at − 80 °C until the day of analysis. White blood cells will be transferred to clean micro-tubes in aliquots, and they will also be kept at − 80 until the day of examination.

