To the best of our knowledge, this will be the first clinical trial being conducted to assess the role of *VDR* polymorphisms in individuals’ responses to vitamin D supplementation through assessing different aspects of cancer etiology, e.g., inflammatory, oxidative stress and metabolic biomarkers, biomarkers associated with cell proliferation, differentiation, damage, apoptosis, and anthropometric measures. Investigating different types of biomarkers will enable us to study the potential mechanisms and pathways through which vitamin D will be involved in cancer etiology and its related milieu. Response to vitamin D based on *VDR* polymorphisms will also be allowing us to scrutinize the gene and environment interactions simultaneously. The following will be the strengths of our study: first, the intervention will be carried out in the cold months, i.e., winter and early spring, when the endogenous synthesis of vitamin D is very low and due to the high prevalence of vitamin D deficiency in Tehran inhabitants [41], more noticeable response to vitamin D supplementation will be anticipated. Second, the results of the present study may illustrate the discrepancies that exist in the findings of different studies regarding vitamin D, VDR, and cancer by considering both genetic and environmental aspects simultaneously. If the response to vitamin D supplementation could be modified by VDR SNPs, determining the distribution of VDR polymorphisms in both breast cancer survivors and healthy populations will provide a new, much-needed insight on individual’s vitamin D requirements to prevent cancer and its related mortality based on the genotypes of these individuals. However, our study will be limited by the relatively small number of SNPs checked, which will likely represent only a small fraction of the variation in the VDR. In addition, the small sample size of the current investigation may result in lower statistical power. Furthermore, the 12-week trial may not be long enough to detect the anti-carcinogenic effects of vitamin D3. Finally, an absence of a control group will make it very difficult to attribute long-term changes in tumor markers to vitamin D3 per se.

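### Hypotheses 1 and 2 credit before–after change to vitamin D, but the single-arm winter-to-spring design cannot separate drug from season, and the calendar windows conflict

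*Protocol article*

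**What the plan says.** The Hypothesis section of the protocol article lists four hypotheses. The first two concern the supplement itself: "Daily supplementation of vitamin D3 will ameliorate circulating 25(OH)D concentrations in breast cancer survivors", and "Daily supplementation of vitamin D3 will improve inflammatory, oxidative stress, and metabolic biomarkers", among other outcomes. The third and fourth concern differences in response between VDR genotype groups and between haplotype groups. The primary and secondary objectives ask for comparisons both within and between those groups.

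There is one arm. The abstract states "One hundred ninety-eight breast cancer survivors will receive 4000 IU of vitamin D3 daily for 12 weeks", and the Intervention section says that "laboratory assessments will be carried out before and after supplementation, and outcomes of interest will be compared between variant" VDR groups. On duration: "The intervention period will be 12 weeks".

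The calendar is described three times:
- Study design: "The intervention period will be limited to the winter months (February, April) and spring months (May, June) to reduce dermal vitamin D synthesis".
- Blood sampling: "Fasting venous blood samples (15 ml) will be taken in spring (April–May) and winter (February–March) from all participants".
- Discussion: the intervention is placed in the cold part of the year, ending in early spring, and this is counted as a strength.

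Statistical analyses adjusts for sun exposure and baseline 25(OH)D, among other covariates. It names no term for season or calendar date. The Discussion concedes that "an absence of a control group will make it very difficult to attribute long-term changes in tumor markers to vitamin D3 per se".

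**The concern.** With no untreated comparator, the effect of supplementation can only be read from the change between the two draws. Season changes over the same interval for every woman. The protocol's own reason for its timing is that skin synthesis of vitamin D is low in the cold months, so synthesis should rise towards the spring draw. For 25(OH)D, the primary outcome, that pushes in the direction of hypothesis 1.

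Two of the four hypotheses, and any causal reading of the within-group half of the objectives, therefore rest on a contrast that cannot separate drug from season. The protocol does not warn of this: it presents the timing as an advantage and limits its no-control caveat to long-term tumor-marker changes. Separately, if the three calendar statements cannot all be met, some final draws will fall outside a stated window.

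**Working it through.** **1. Do treatment and season change together for everyone?** Blood sampling names February–March and April–May, for all participants. The draws are 12 weeks (84 days) apart. A baseline in February–March with follow-up in spring fits that interval. The reverse order, a spring baseline with follow-up the next winter, would take far longer than 12 weeks. So each woman's baseline is in winter and her final draw in spring, and no contrast within the study separates the two influences.

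**2. Dates (non-leap year, start + 84 days)**

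| Baseline draw | Final draw | Inside April–May? |
|---|---|---|
| 1 February | 26 April | yes |
| 8 March | 31 May | yes |
| 9 March | 1 June | no |
| 31 March | 23 June | no |

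Baselines on 9–31 March lie inside the winter sampling window, but their final draws fall on 1–23 June. That is outside the Blood sampling window and inside the Study design span, which runs to June. The Study design sentence also labels April as winter and omits March, and its May–June end does not match the Discussion's early spring.

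**3. Sample size used below.** The plan's figure reproduces: 3 × 55 = 165, and 165 × 1.2 = 198. The expected number of completers is therefore 165, or 198 × 0.8 ≈ 158 if 20% of those recruited are lost.

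**4. How small a seasonal shift would look like a drug effect?** The documents give no SD and no seasonal figure, so the shift *s* (in SD of change) is an assumption. For a paired two-sided 5% test with zero drug effect, the probability of significance is Φ(s√n − 1.96) + Φ(−s√n − 1.96). With n = 165, √n = 12.85:

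| s (assumed) | s√n | n = 165 | n = 158 |
|---|---|---|---|
| 0.10 | 1.28 | 25% | 24% |
| 0.15 | 1.93 | 49% | 47% |
| 0.20 | 2.57 | 73% | 71% |
| 0.30 | 3.85 | 97% | 97% |

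**5. Does adjusting for sun exposure help?** Simulation with 2,000 trials per scenario, n = 165, zero drug effect, and a mean seasonal shift of 0.2 or 0.3 SD acting through change in sun exposure (assumed). The noisy measure is assumed to have reliability 0.5.

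| Covariate | False drug effect, s = 0.2 | s = 0.3 |
|---|---|---|
| Baseline sun exposure only | 71% | 96% |
| Change in exposure, noisy measure | 14% | 27% |
| Change in exposure, perfect measure | 5% | 6% |

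A baseline covariate cannot remove a shift shared by all women. The Intervention section's list of before-and-after assessments omits sun exposure, and the Sun exposure assessment section gives no timing for its questionnaire.

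**6. Genotype contrast.** In the same simulations, with genotypes drawn at the quoted minor allele frequency of 0.3285, the test between three genotype groups rejected in 5.4% and 5.2% of trials. A seasonal shift common to all groups cancels.

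**The case against.** The strongest reply is that this is a study of response by VDR variation, and season does not bias that comparison. This stands, provided enrolment date is unrelated to genotype. A reader might infer that the whole trial is confounded; the documents do not support that.

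Several other strong readings also fail:
- **That the plan ignores sunlight.** It does not; sun exposure is a named covariate. What is unstated is whether the questionnaire is repeated, and silence in a condensed article does not show that it is given only once.
- **That the protocol claims to eliminate skin synthesis.** Study design speaks only of reducing it.
- **That hypotheses 1–2 would be declared confirmed by season alone.** Statistical analyses names no paired before–after test, and the objectives are phrased as comparisons. The percentages in step 4 therefore show sensitivity and do not predict the trial's result.
- **That season favours hypothesis 2 as well.** The rationale about skin synthesis concerns vitamin D only. No seasonal direction is given for the other markers.
- **That excluding women with high vitamin D creates material regression to the mean.** The documents give no figure. They also cite widespread deficiency in Tehran, so the exclusion may remove few women.
- **That a fixed share of women will miss the sampling window.** That depends on how starts are spread; enrolment closing by 8 March would meet it.

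Finally, the Discussion does admit the missing control group. The admission does not reach 25(OH)D or the 12-week changes that hypotheses 1–2 concern.

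**Conclusion.** The point holds for hypotheses 1–2 and for causal use of the within-group comparisons. Because every woman moves from winter to spring while on treatment, the overall change cannot be attributed to the supplement. For 25(OH)D the seasonal bias runs in favour of the hypothesis. For the other biomarkers attribution is equally unsupported, with unknown direction. Part of the 25(OH)D rise may well be a true drug effect; the design cannot say how much.

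The size of the bias is not derivable from the documents. On the assumed range, shifts of 0.15 to 0.20 SD of change would be enough to make a before–after test significant in about half to three quarters of trials with no drug effect. The planned sun-exposure adjustment can remove part of this only if change in exposure is measured. Hypotheses 3–4 are largely unaffected.

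The calendar conflict needs no assumption beyond 84 days between draws, and the passages must be reconciled.

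**What to change.** 1. Restate hypotheses 1–2 and the within-group objectives as change from baseline over a winter-to-spring supplementation period, without attributing the change to vitamin D.
2. Widen the no-control caveat in the Discussion to cover 25(OH)D and the 12-week biomarker changes.
3. Keep the between-genotype and between-haplotype contrasts as the confirmatory question.
4. Reconcile the calendar statements in Study design, Blood sampling and the Discussion, so that the baseline and final sampling windows are compatible with the stated 12 weeks.
5. As a secondary step for precision, give the existing sun-exposure questionnaire at both visits, and include change in the index and the baseline draw date in the change models. State that this does not restore causal attribution: draw date varies between women and cannot remove a shift they all share, and a noisy exposure measure removes only part of it.

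The cost is rewording, one repeated questionnaire and two covariates. The sponsor gives up a causal claim that the design cannot support. No new arm is needed for the genotype and haplotype questions.

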## Methods/Design

### Study design

This will be a 3-month clinical trial conducted on breast cancer survivors to assess the potential effects of vitamin D3 supplement on plasma vitamin D levels, inflammatory and antioxidant biomarkers, and factors associated with cell proliferation, differentiation, damage, and apoptosis based on polymorphic variation in VDR gene. The intervention period will be limited to the winter months (February, April) and spring months (May, June) to reduce dermal vitamin D synthesis. The current study will be accomplished by collaboration between the Faculty of Nutrition Sciences and Food Technology and the National Nutrition and Food Technology Research, the Cancer Research Center, and the Research Institute for Endocrine Sciences, Shahid Beheshti University of Medical Sciences.

### Participants

This study will be conducted on women previously diagnosed with invasive or in situ breast cancer, whose cancers were confirmed by pathological examination. Patients admitted to Shohadaye Tajrish hospital and its associated clinics in Tehran who had been diagnosed with cancer for at least the past six months and their treatments, including surgery, radio, and chemotherapy had been completed will be requested to participate in the study.

